### In-depth qualitative outcome data

A qualitative process evaluation will be conducted using semistructured interviews to provide understanding of the study delivery and its potential scale-up. All participants who complete the questionnaires will be given the opportunity to volunteer to be interviewed. We aim to interview patients and carers at baseline and intervention, whereas professionals will be interviewed at all three stages (baseline, training and intervention). All participants (including children) will be remunerated in vouchers for participation.

### Data analysis plan

We will be following the published extension to Consolidated Standards of Reporting Trials (CONSORT)^27^ when reporting the results of this feasibility study. As this is a feasibility study, no formal sample size calculation has been conducted. Our targeted sample size (n=90, phase 1; n=40, phase 2) should be large enough to consider the practicalities of recruitment and delivering the interventions.

Descriptive statistics for intervention feasibility, acceptability and appropriateness will be presented. A chart of participant flow during the whole study will be plotted (CONSORT flow chart), which will include information on the retention/withdrawal (including timing and reasons) of wards during the evaluation. We will also present the number of health practitioners who completed the questionnaires and interviews against the number of professionals working in the wards during the evaluation, and the number of patients/carers completing the questionnaires/interviews against those discharged during the duration of the study. We will also conduct basic psychometric analyses to verify the scale structure and internal consistency of the used questionnaires. For explorative purposes, we will examine differences between the three measures completed by patients recruited during the baseline phase and the measures completed by the patients during the intervention phase. Before starting with the analyses, we will examine if the data are normally distributed. If the data are normally distributed, parametric tests will be used, otherwise non-parametric tests will be used. The significance level for all analyses will be p≤0.05. The data analyst will be blinded to the phase allocation (baseline or intervention phase).

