**Methods and analysis:**

Two uncontrolled before-and-after feasibility studies, where all participants will receive the intervention. We will examine the feasibility and acceptability of the SAFER-MH in inpatient mental health settings in patients aged 18 years or older who are being discharged and the feasibility and acceptability of the SAFER-YMH intervention in inpatient mental health settings in patients aged between 14 and 18 years who are being discharged. The baseline period and intervention periods are both 6 weeks. SAFER-MH will be implemented in three wards and SAFER-YMH in one or two wards, ideally across different trusts within England. We will use quantitative (eg, questionnaires, completion forms) and qualitative (eg, interviews, process evaluation) methods to assess the acceptability and feasibility of the two versions of the intervention. The findings will inform whether a main effectiveness trial is feasible and, if so, how it should be designed, and how many patients/wards should be included.

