### Eligibility criteria

#### Eligible sites

Eligible sites will be acute adult inpatient mental health wards. As this is a feasibility study, we will aim to test on a variety of wards (ie, female, male or mixed).

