### Quantitative outcomes

These will be measured in the baseline phase and intervention phase with different patients. To assess patients’ and carers’ perspectives, the quantitative outcomes will be measured using paper/online versions of a series of questionnaires which include: (1) the EQUIP-PROM, a 14-item co-designed measure to assess patient/carer views of care planning in mental health,^23^ (2) a short four-item version of the CTM^24^ and (3) the five novel items assessing the safety of mental healthcare transitions^9^; properties of these outcome measures can be found in table 2.

**Table 2 T2:** Properties of outcome measures used

Validated outcome measure	Psychometric properties	Scoring system
EQUIP	Scale has acceptable scalability (Ho=0.69), reliability (alpha=0.92), fit to the Rasch model (χ2(70)=97.25, p=0.02), and no differential item functioning or locally dependent items.	It uses a 5-point Likert scale ranging from 1=‘strongly disagree’ to 5=‘strongly agree’, with a middle neutral value meaning ‘neither agree nor disagree’. Higher scores indicate higher-perceived quality care planning.
CTM-4	The Cronbach’s alpha for CTM-4 is 0.85.	The CTM items are rated on a 4-point Likert scale ranging from 1=‘strongly disagree’ to 4=‘strongly agree’, with a fifth response being ‘don’t know/don’t remember/not applicable’. The summarised score (excluding the ‘not applicable’ scores) is computed as the total sum divided with the number of answered items, minus 1 and multiplied by 100 to get a total score (0–100) for each respondent. Higher scores indicate better patient/carer experience of care transitions.

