The feasibility study will include paper and pdf editable versions of the intervention documents (eg, social information capture and patient written discharge plan), which have not been integrated into the trusts’ electronic records yet. Understanding how the intervention documents will fit within the trusts’ electronic records is a key learning task of this feasibility study, which will potentially inform a larger randomised controlled trial (RCT). Similarly, as this is a feasibility study, we are mostly interested in the completion rate of the scales, and the views by patients/carers and staff members about the relevance of these measures to their experiences in relation to hospital discharge. We would not have enough power to generate any meaningful quantitative analysis using our outcome measures and we will not collect quantitative data around readmission rates or adverse events at this stage. However, if this study produces convincing evidence that the intervention is feasible/acceptable, we will request further funding to conduct an RCT, which will involve more extensive data collection (including routinely collected data on readmissions and adverse events) and a comprehensive quantitative analysis plan for a definitive RCT. There is considerable evidence about the importance of community follow-up of patients at post-discharge. Although this is a pre-discharge intervention, there is growing evidence that continuity of care and post-discharge follow-up of patients could enhance safety. Depending on the feedback that we will obtain from the intervention recipients/deliverers during this feasibility study, we will explore whether further adaptations are needed to include post-discharge elements in the intervention protocol.

Improving safety at mental health discharge is a key concern for patients, professionals and policymakers. Therefore, interventions aiming to improve knowledge sharing, shared decision-making and involvement of patients/carers are considered preferable.^21 23 32^ This study will determine the feasibility and acceptability of a multicomponent intervention to improve involvement of patients and/or carers in discharge planning. This will provide evidence for the acceptability of the SAFER-MH and SAFER-YMH to inform future improvements to scale to an RCT, with concurrent process evaluation and economic evaluation.

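### The exploratory before/after comparison is set up as p≤0.05 tests chosen by a normality check, although the article itself says these data cannot carry such an analysis; fixed mean differences with intervals would serve better

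*Protocol article*

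**What the plan says.** In this note, period means baseline or intervention; the article's phases 1 and 2 are called the adult and the youth study.

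- Protocol article, Data analysis plan, on purpose: "For explorative purposes, we will examine differences between the three measures completed by patients recruited during the baseline phase", set against those of patients in the intervention period.
- Same section, on choice of test: "If the data are normally distributed, parametric tests will be used, otherwise non-parametric tests will be used".
- Same section, on the decision rule: "The significance level for all analyses will be p≤0.05".
- Same section, on size: "Our targeted sample size (n=90, phase 1; n=40, phase 2) should be large enough to consider the practicalities of recruitment". It states that no formal calculation was made. Table 1 gives 45 patient/carer respondents in each period.
- Quantitative outcomes, on the groups: "These will be measured in the baseline phase and intervention phase with different patients". The comparison is therefore unpaired.
- Discussion, on what the data can support: "We would not have enough power to generate any meaningful quantitative analysis using our outcome measures".
- Abstract, Methods and analysis: the findings are to inform whether a main trial is feasible and, if so, "how it should be designed, and how many patients/wards should be included".

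**The concern.** The threshold and the test-selection rule are written into the article, so this is not a matter of detail left to another document. They conflict in spirit with the Discussion: one section fixes a yes/no rule for all analyses, and another says that the same measures cannot support a meaningful analysis. With low power, a non-significant result says almost nothing, and an isolated significant one may well be chance.

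The normality check adds a second problem. If it passes, means are compared; if it fails, ranks are. The quantity compared is then decided by the data and may differ between measures, or between the adult and the youth study for the same measure. A rank test does not itself yield a mean difference with an interval, which is the form that main-trial planning can use.

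At stake is how the results are read and carried forward. Designing a main trial calls for SDs and for differences with their uncertainty, and the stated rule for this comparison names only tests and a threshold.

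**Working it through.** **Inputs.** Alpha is 0.05 (Data analysis plan); two-sided is assumed, as the article does not say. The adult study has 45 per period (Table 1), which agrees with the target: 45 + 45 = 90. That 45 covers patients and carers, so patients alone may be fewer. For the youth study only the total of 40 is given, so 20 per period is an assumption. There are three patient measures per study. The Procedure text has the Care Transitions Measure at baseline but Table 1 omits it there; these need reconciling before three comparisons are possible. No effect size, SD or power target is stated, so there is no calculation of the plan's own to reproduce, and results are in SD units.

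**Power.** Two-sample t-test with n per period, df = 2n − 2, noncentrality d·√(n/2):

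| n per period | df | Power at 0.3 SD | Power at 0.5 SD | Difference with 80% power |
|---|---|---|---|---|
| 45 | 88 | 29% | 65% | 0.60 SD |
| 20 (assumed) | 38 | 15% | 34% | 0.91 SD |

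By the normal approximation, 80% power would need 63 per period at 0.5 SD and 175 at 0.3 SD. The Discussion's statement about power is thus correct.

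**False positives.** Three tests in one study: 1 − 0.95³ = 0.143. This assumes independence. The same patients complete all three questionnaires, so the scores are probably correlated and 14% is best read as an upper figure.

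**Normality check.** In simulation (10,000 runs; Shapiro-Wilk, then t or Mann-Whitney; normal, skewed and coarse score distributions), the type I error of the two-step procedure was 0.048 to 0.056. The check hardly disturbs the error rate. Its fault is the unfixed quantity.

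**What estimation would give.** Half-width of the 95% CI = t(0.975, df)·√(2/n):
- n = 45: 1.987 × 0.2108 = 0.42 SD
- n = 20: 2.024 × 0.3162 = 0.64 SD

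**Ward mix, under assumptions.** The same wards supply both periods, so stable ward differences bias the comparison only if the ward mix of respondents shifts. Suppose three ward means of 0, 0.4 and 0.8 SD and a mix moving from 20/15/10 to 10/15/20:

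(15×0.4 + 20×0.8)/45 − (15×0.4 + 10×0.8)/45 = 22/45 − 14/45 = 0.18 SD with no true effect.

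Simulated false-positive rates with 45 per period, stable ward effects and ICC 0.02 to 0.10 (6,000 runs each):

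| Ward mix, baseline vs intervention | Unadjusted t-test |
|---|---|
| 15/15/15 vs 15/15/15 | about 0.045 |
| 20/15/10 vs 10/15/20 | 0.057 to 0.069 |
| 25/15/5 vs 5/15/25 | 0.077 to 0.151 |

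With ward as a fixed effect the rate was 0.046 to 0.055 throughout. When 20% of the ward variance was specific to the period, the adjusted rate was 0.05 to 0.09, so a ward term does not remove ward-by-time drift.

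**Between-ward variation.** Take 3 wards × 30 and an assumed observed ICC of 0.05. Then F = 1 + 30 × 0.05/0.95 = 2.58. The 97.5% points are 3.85 (2, 87 df) and 39.5 (87, 2 df), so the limits on the F scale are 0.670 and 101.8. With (F − 1)/(F + 29), the ICC limits are −0.01 and 0.77, that is, about 0 to 0.77.

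**The case against.** The strongest reply is that the article already guards against misreading. The comparison is labelled exploratory, Outcomes says the design gives only a first indication about the measures, the lack of a control is listed as a limitation, and the power limit is disclosed. Moving on to a randomised trial is tied to evidence of feasibility and acceptability, not to these p-values. Choosing a test does not stop anyone tabulating means and SDs, and recruitment and completion figures are planned separately. All of this stands and limits the harm. It does not explain why a threshold is set for all analyses when the authors say the result would not be meaningful, and it leaves the quantity compared open.

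Two stronger readings are tempting and are not supported.

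- A reader might infer that the plan pools different wards and so produces ward-confounded results, since the sponsor's team writes "we will aim to test on a variety of wards (ie, female, male or mixed". The article does not say that wards are pooled; it is silent on ward, and a ward term may sit in the full plan. Confounding also needs a shift in ward mix between periods, and it cannot arise between wards if the youth study uses a single ward, which the article allows.
- A reader might infer that the Abstract promises an estimate of between-ward variation. It says only that the findings will inform the number of wards, which recruitment and completion data can help with.

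Adding all six tests over both studies (1 − 0.95⁶ = 26%) would also overstate the matter, because these are two separate studies.

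**Conclusion.** The point holds in a limited form and is worth a change of wording. The stated rule leads to significance decisions that carry little information: only differences of about 0.60 SD (adult study) or 0.91 SD (youth study) have 80% power, and up to 14% of null studies would show at least one p≤0.05. It also leaves the choice between means and ranks to the data. These figures rest on two-sided tests, full recruitment, an even 20/20 split in the youth study and, for the 14%, independent measures. The normality check is not a type I error problem. Ward imbalance is a conditional risk against which a ward term is cheap protection, not a demonstrated bias. At most, one may note that three wards cannot give a usable ICC for the main trial.

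**What to change.** In the Data analysis plan, replace the sentences on the normality check, the choice of test and p≤0.05 with wording such as:

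> For each patient measure we will report the mean and SD in each period and the mean difference between periods with a 95% confidence interval, using a bootstrap interval if the scores are skewed. Where a study has more than one ward, the difference will come from a linear model with period and ward as fixed effects. No significance threshold will be applied and no conclusion on effectiveness will be drawn.

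The mean difference then stays the target whatever the shape of the data; only the way the interval is obtained changes. It would help to add that the ward term covers a change in ward mix between periods, if one occurs, but not changes within wards over time, and that any ICC for the main trial should not rest on three wards alone.

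The cost is small: no new data, no p-values to quote, and up to two degrees of freedom used for ward.

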### Qualitative analysis

We will use a framework approach to qualitative analysis, to inductively code and organise the data and identify emerging themes from the interviews. The frameworks will be based on three underpinning theoretical frameworks commonly used in similar research: the Conceptual Framework for Implementation Fidelity (5 domains), Theoretical Framework of Acceptability^28^ and the Theoretical Domains Framework (14 domains). The coding process will follow these steps:

Familiarisation (researchers immersing themselves in the data).Identifying a thematic framework (to generate an index of data based on a priori questions and issues raised by participants).Indexing (applying thematic framework to the data using NVivo software).Charting (rearranging data in line with thematic framework).Mapping and interpretation (using the charts to define concepts, map the range and nature of phenomena and find associations between themes).

### Integration of quantitative and qualitative data

The quantitative and qualitative results will be initially considered separately but we aim to examine how they converge or differ when presenting the overall conclusions.^29^ Furthermore, the qualitative data collected across the two studies will be used to help explain or elaborate on the quantitative data.^29^

### Patient and public involvement

This study has a patient and public involvement service-user co-researcher who has been involved in the design and delivery of the study (AG). Patient and public involvement has been integral to this study and the development of the intervention, which has been based on a series of stakeholder consultations, workshops and consensus methods.^9 10 21 30^ A core group of five patient and public involvement representatives forms a steering committee for this study.

## Ethics and dissemination

Ethical approval was obtained from the NHS Cornwall and Plymouth Research Ethics Committee and Surrey Research Ethics Committee (reference: 22/SW/0096 and 22/LO/0404, respectively).

The study findings will be shared with participating inpatient sites in a range of ways to engage different audiences, as well as via presentations at national and international conferences, and published in open-access peer-reviewed journals. Findings will be presented at a workshop for patients and carers, and a vlog will be created.

## Discussion

This study aims to understand how to improve information sharing and capture between services during patient discharge from psychiatric hospitals to community services. Extensive stakeholder engagement with patients, carers, mental health professionals and academics has informed the intervention refinement and study co-design. We propose a pragmatic approach to test the feasibility and acceptability of a novel intervention, which will add value to the evidence base about how information sharing/capture and patient/carer knowledge and involvement around discharge improve patient safety, healthcare utilisation and other important patient outcomes.

The findings will have to be interpreted and evaluated considering the limitations of the study design. For example, this is a pre/post uncontrolled study and the potential influence of inpatient settings cannot be controlled for through randomisation. Another limitation is that the interventions have only been developed in English and future work will need to explore how to culturally adapt it. Furthermore, some elements of the intervention may not be suitable for individuals with dementia who often occupy mental health inpatient beds^31^; however, funding has been obtained to develop this in future work. Finally, the intervention sites will be identified through collaborators, so selection bias must be considered.

The feasibility study will include paper and pdf editable versions of the intervention documents (eg, social information capture and patient written discharge plan), which have not been integrated into the trusts’ electronic records yet. Understanding how the intervention documents will fit within the trusts’ electronic records is a key learning task of this feasibility study, which will potentially inform a larger randomised controlled trial (RCT). Similarly, as this is a feasibility study, we are mostly interested in the completion rate of the scales, and the views by patients/carers and staff members about the relevance of these measures to their experiences in relation to hospital discharge. We would not have enough power to generate any meaningful quantitative analysis using our outcome measures and we will not collect quantitative data around readmission rates or adverse events at this stage. However, if this study produces convincing evidence that the intervention is feasible/acceptable, we will request further funding to conduct an RCT, which will involve more extensive data collection (including routinely collected data on readmissions and adverse events) and a comprehensive quantitative analysis plan for a definitive RCT. There is considerable evidence about the importance of community follow-up of patients at post-discharge. Although this is a pre-discharge intervention, there is growing evidence that continuity of care and post-discharge follow-up of patients could enhance safety. Depending on the feedback that we will obtain from the intervention recipients/deliverers during this feasibility study, we will explore whether further adaptations are needed to include post-discharge elements in the intervention protocol.

Improving safety at mental health discharge is a key concern for patients, professionals and policymakers. Therefore, interventions aiming to improve knowledge sharing, shared decision-making and involvement of patients/carers are considered preferable.^21 23 32^ This study will determine the feasibility and acceptability of a multicomponent intervention to improve involvement of patients and/or carers in discharge planning. This will provide evidence for the acceptability of the SAFER-MH and SAFER-YMH to inform future improvements to scale to an RCT, with concurrent process evaluation and economic evaluation.
